#### Methods of statistical analysis

Statistical analysis is based on the International Conference on Harmonization Guidelines “Structure and Content of Clinical Study Reports” and “Statistical Principles for Clinical Trials”. The primary analysis set for all efficacy outcomes will be the intention-to-treat (ITT) population, while the per-protocol (PP) population will be used for sensitivity analyses.

The primary endpoint ORR will be evaluated by reporting absolute and relative frequencies for both treatment groups. For group A, a binomial test will be conducted at a one-sided significance level of α = 0.05 in order to assess if the ORR exceeds 19%. Furthermore, one-sided 95%-confidence intervals will be calculated for the ORR in both groups.

For the secondary time-to-event outcomes OS and PFS, median survival times and 1-year rates will be given with 95% confidence intervals and Kaplan-Meier curves will be calculated for both treatment groups.

Descriptive sub-group analyses with regard to PD-L1 status will be conducted assessing the primary and secondary outcomes separately for the patient strata PD-L1 high/low (e.g. cutoffs 1, 5, and 10%) by reporting the same statistical measures as described before for both treatment groups.

Safety analysis will be done for all patients who received at least one dose of study medication and according to the treatment actually received. It includes a tabulation of relative and absolute frequencies for adverse and serious adverse events. After 25 patients have been treated in group A, a descriptive safety report will be generated and evaluated by the Data Safety Monitoring Board.

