#### Secondary objectives

Secondary objectives are to collect information on feasibility, safety and tolerability of nivolumab by measurement of incidence and severity of adverse events (AEs) and specific laboratory abnormalities in all treated subjects by treatment strata and groups. Additionally, further efficacy data will be collected in patients without necessity of radiotherapy as well as information on individual, patient reported and investigator-assessed quality of life.

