Treatment emergent adverse events (AEs) according to common terminology criteria for adverse events (CTCAE) version 4.03 will be recorded in the eCRF using a recognized medical term or diagnosis that accurately reflects the event. Adverse events will be assessed by the investigator for severity, relationship to the investigational product, possible etiologies, and whether the event meets criteria of a serious adverse event (SAE) and therefore requires immediate notification to the CRO. AEs and SAEs will be recorded during the entire study duration, including the regular 30 day safety follow-up period after the end-of-treatment (EOT) visit. Subsequently, subjects will be followed for ongoing study treatment-related adverse events until resolved, return to baseline or deemed irreversible, until lost to follow-up, or withdrawal of study consent. Furthermore, only new and ongoing SAEs deemed related to study treatment will be collected and recorded for an additional 70 days. The investigator is responsible for ensuring that all adverse events observed by the investigator or reported by patient are properly captured in the patients’ medical records. During the course of the study all AEs and SAEs should be proactively followed up for each subject. Every effort should be made to obtain a resolution for all events, even if the events continue after discontinuation/study completion.

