#### Immunotherapy

Nivolumab will be given every two weeks at a dose of 240 mg to be administered as a 60 min IV infusion. Treatment regimen depends on study group: in study group A, nivolumab will be given on day 1 of the first cycle and continued to be given every two weeks. The first fraction of radiotherapy has to be delivered within 72 h after cycle 1 day 1.

In study group B, nivolumab will be given on day 1 of the first cycle and continued to be given every two weeks.

In both groups, nivolumab treatment will be continued until progression or until limiting toxicities occur.

Nivolumab administration will be delayed in case of any AE, laboratory abnormality or intercurrent illness which, in the judgment of the investigator, warrants delaying the dose of study medication.

Subjects may continue to receive treatment beyond confirmed progression in the absence of clinically significant deterioration and if investigators expect continual benefit from the treatment. For statistical analyses, these subjects will be considered to have investigator-assessed progressive disease at the time of the initial progression event.

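### The adverse event percentages planned for each group depend on time on nivolumab, which may differ between the non-randomised groups; a fixed-window incidence and a rate per patient-month should stand beside them

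*Protocol article*

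**What the plan says.** **Capture.** The Study procedures section states: "AEs and SAEs will be recorded during the entire study duration, including the regular 30 day safety follow-up period after the end-of-treatment (EOT) visit". Two extensions follow. For serious events, "only new and ongoing SAEs deemed related to study treatment will be collected and recorded for an additional 70 days". For events already under way, "subjects will be followed for ongoing study treatment-related adverse events until resolved, return to baseline or deemed irreversible". Table 2 agrees: AEs and SAEs are marked through treatment and safety follow-up, but not in survival follow-up.

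**Treatment length.** The Immunotherapy section states: "In both groups, nivolumab treatment will be continued until progression or until limiting toxicities occur". The same section allows treatment beyond progression where the investigator expects benefit.

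**Analysis.** The safety population is every patient with at least one dose, analysed as treated. Of the safety analysis, the Methods of statistical analysis section says: "It includes a tabulation of relative and absolute frequencies for adverse and serious adverse events". It gives OS and PFS Kaplan-Meier curves, medians and 1-year rates.

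**Use.** The Secondary objectives ask for AE incidence and severity "in all treated subjects by treatment strata and groups". The abstract's Discussion says that the study will investigate toxicity of nivolumab both with and without radiotherapy. The closing summary of the Discussion puts safety and feasibility of the combined approach first among three goals.

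**The concern.** The period in which a new AE of any kind can be recorded equals time on nivolumab plus about one month. Time on nivolumab is an outcome: it depends on progression, toxicity and the investigator's judgement about continuing. A crude percentage counts a patient observed for three months and one observed for a year as equal denominators.

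The groups are not randomised, and two features of the plan could pull exposure apart. The sample size section hypothesises 35% response in group A and assumes 19% in group B, which would lengthen exposure in A. Group A is also selected for needing palliative radiotherapy, which may shorten it.

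Efficacy outcomes with unequal follow-up get time-to-event methods, while the AE summary that is named takes no account of follow-up time. At stake is how the two columns of the AE table are read. A gap could reflect observation time alone, and a real excess with the combination could be hidden.

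**Working it through.** The protocol gives no expected AE rate, treatment duration or AE percentage, so there is no safety figure of its own to reproduce. The check asks how far crude percentages can move with exposure. Apart from the capture windows and the 35% and 19% response rates, every input is an assumption.

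**Model.** Constant hazard *h* per month for a first event; exponential time on drug with mean *m* months; capture for a further *w* months. Crude risk = 1 − exp(−*hw*) / (1 + *hm*).

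**1. Equal hazards, exposure differing only through response.** Assume a mean of 12 months on drug for responders and 2 for non-responders, with *w* = 1.
- Mean capture, A: 0.35 × 12 + 0.65 × 2 + 1 = 6.5 months. B: 0.19 × 12 + 0.81 × 2 + 1 = 4.9 months.
- *h* = 0.05, A: 1 − 0.9512 × (0.35/1.6 + 0.65/1.1) = 23.0%.
- *h* = 0.05, B: 1 − 0.9512 × (0.19/1.6 + 0.81/1.1) = 18.7%.
- *h* = 0.10: 36.6% (A) against 31.1% (B).

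The true hazard ratio is 1.0, yet the table shows an excess in A of 4.3 points at *h* = 0.05.

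**2. True hazard ratio 1.5 against A, with A shorter on drug.** *w* = 1; B has hazard *h* and a mean of 6 months.

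| *h* in B | A, mean 3 months | B, mean 6 months |
|---|---|---|
| 0.05 | 1 − exp(−0.075)/1.225 = 24.3% | 1 − exp(−0.05)/1.30 = 26.8% |
| 0.10 | 1 − exp(−0.15)/1.45 = 40.6% | 1 − exp(−0.10)/1.60 = 43.4% |

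The excess is hidden and slightly reversed. With a mean of 4 months in A and *h* = 0.05, A is 1 − exp(−0.075)/1.30 = 28.6% against 26.8%. The sign is then right, but the excess is only 1.8 points.

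**3. Effect of the 70 further days for related SAEs.** Here time on drug is given by its median, so *m* = median / ln 2. Take *h* = 0.05. Between a median of 2 and a median of 6 months on drug, crude risk rises from 16.8% to 33.6% with a 30-day tail, and from 25.8% to 40.8% with a 100-day tail. The longer tail weakens the dependence on exposure but does not remove it.

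**4. What the added displays would return.** In this model, incidence by 12 weeks (84/30.44 = 2.76 months) is 1 − exp(−2.76*h*), if end of capture is handled as censoring unrelated to the event. In scenario 1 at *h* = 0.05 it is 12.9% in both groups. In scenario 2 it is 1 − exp(−2.76 × 0.075) = 18.7% in A against 12.9% in B. First events per patient-month return the ratios 1.0 and 1.5. This is exact only because the model has a constant hazard and independent censoring.

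**The case against.** The strongest reply is that this is a condensed article. Exposure-adjusted tables commonly sit in the analysis plan, which is not shown, and the safety sentence says only what the analysis includes. That stands: a reader might infer that exposure-adjusted analyses are ruled out, and the text does not say so. The point survives because the section is not silent. It names a measure for AEs, and that measure varies with exposure.

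Three other strong readings also fail.
- **That safety capture simply stops at 30 days.** It does not. New and ongoing related SAEs are collected for 70 days more, and ongoing related AEs are followed to resolution. The 30-day limit applies to new events that are non-serious or unrelated.
- **That a planned A-versus-B safety test is biased.** None is planned. The only test is of group A's response rate against 19%, and safety is descriptive. The risk lies in interpretation.
- **That exposure is known to differ, in a known direction.** No duration is given for either group. The two influences named above oppose each other and might cancel, and treatment beyond progression loosens the link to progression.

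On size, with 65 per group the standard error of the 24.3% versus 26.8% difference is √[(0.243 × 0.757 + 0.268 × 0.732)/65] ≈ 7.6 points, against a difference of 2.5. For 23.0% versus 18.7% it is about 7.1 points. The illustrated distortions are therefore smaller than sampling error. Scenario 2 also lets radiotherapy raise the hazard for the whole time on drug, whereas radiotherapy starts within 72 hours of the first dose and is expected to last no longer than 2 weeks. Acute effects would fall largely inside every patient's capture period. This stands as a limit on size. It also favours an early-window table, because a crude table mixes early events with late ones.

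Finally, exposure adjustment cannot make the groups comparable, since they are defined by need for radiotherapy. That is correct and should be stated with the results.

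**Conclusion.** The point holds as a modest, inexpensive improvement to the safety analysis. It does not show an invalid test. Capture of all AEs is tied to a treatment length driven by progression or toxicity, so crude frequencies by group depend on time on nivolumab, and that time may differ between non-randomised groups.

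The size and direction of any distortion cannot be determined from the protocol. The illustrations (23.0% against 18.7% at equal hazards; 24.3% against 26.8% at a true hazard ratio of 1.5) rest on assumed durations, constant assumed hazards and a one-month tail. They show that a spurious gap and a masked excess are both possible; they do not predict either. If the full analysis plan already specifies exposure-adjusted or fixed-window displays, a reference to it closes the point.

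**What to change.** In the Methods of statistical analysis section, keep the crude AE and SAE table and add two displays by group:

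- **(a) Fixed-window incidence.** AE and SAE incidence within a common early window from first dose that contains all radiotherapy, for example 12 weeks. Use cumulative incidence with death as a competing event, and state how end of capture is handled. Where treatment stopped for toxicity or progression, end of capture may be related to AE risk, so the assumption should be written down.
- **(b) Rates.** First events per patient-month of AE capture with 95% confidence intervals. The denominator should match the window: 30 days after the end-of-treatment visit for all events, and 70 days more where related SAEs are counted.

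Base any descriptive statement on toxicity with versus without radiotherapy on these displays, and state that they do not remove confounding by indication.

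The cost is two more tables, built from first and last dose dates and AE onset dates in the eCRF. The rates in (b) assume a roughly constant hazard; (a) does not, which is the reason to show both.

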### Trial status

The first patient was enrolled in March 2017. The FORCE trial is currently recruiting patients.

## Discussion

Lung cancer is the most common cause of cancer death worldwide with approximately 85% of patients suffering from NSCLC. Until recent years, treatment of NSCLC has been limited to chemotherapy with a sparse impact on median progression-free survival times ranging from 3 to 4 months. The therapeutic concept of restoring the patients’ antitumor immunity by inhibition of immune checkpoints such as PD-1/PD-L1 has been a groundbreaking advancement. Currently, PD-1/PD-L1-targeting checkpoint inhibition has even advanced up to 1st-line treatment, either as a monotherapy or in combination with chemotherapy. Despite this important progress a crucial remaining question is how T-cell-mediated antitumor immune responses upon checkpoint inhibition can be activated in non-responders, which account for approximately half of the patients [3, 4, 6, 22].

Palliative radiotherapy is a frequent therapeutic necessity in metastatic lung cancer. Preclinical studies, single patient reports, and retrospective analysis have shown that the combination of immunotherapy and radiotherapy can exert independent antineoplastic effects and simultaneously promote and perpetuate the radiation-associated abscopal effect [19, 23–25]. However, prospective studies investigating these observations are scarce. In a large phase III trial with patients with metastatic prostate cancer, no benefit of cytotoxic T-lymphocyte-associated antigen-4 (CTLA-4) blockade after radiotherapy was observed [26]. Consistent with these results, all reported preclinical and clinical cases of the combination have occurred with radiation therapy given either concomitantly or following CTLA-4 blockade [27]. Thus, it is a rational approach to prospectively investigate the potential benefit of PD-1/PD-L1 blockade concurrent with radiotherapy. This trial aims to recruit patients into group A with a clinical necessity for a radio-oncologic treatment. The appropriate palliation of metastatic disease is a governing treatment goal in these patients and must be performed with diligence. Therefore, no dose finding for the radiation dose will be performed since the risk of sub- or supratherapeutic dose regimens cannot be justified ethically or clinically. The FORCE trial will employ a radiotherapy regimen, which on its own is demonstrably efficacious and safe [28].

The fractionation regimen of 5 × 4 Gy (total dose 20 Gy) aligns with current standard-of-care practices. Compared to more hypofractionated regimens (i.e. less fractions at higher single doses), the FORCE regimen reduces the risk for re-irradiations to become necessary for symptom control (FORCE 10% vs other regimens 23%) [29]. Furthermore, higher single doses (i.e. 1 × 8 Gy) are associated with an increased incidence of pathologic bone fractures (3.2% vs. 2.8%) or spinal compression events (2.8% vs. 1.9%) [28].

The hypofractionated dose regimen chosen for radiotherapy in this trial is known to augment antigen presentation to cells of the anti-tumoral immune system and augment adaptive upregulation of PD-L1 by tumor cells [30, 31]. Compared to less hypofractionated regimens (e.g. 10 × 3 Gy) the FORCE regimen significantly reduces the treatment duration, hence allows to reach the treatment goal of local control of metastasis faster without compromising general patient safety.

Due to the scarcity of data from prospective clinical trials addressing radio-immunological treatments in NSCLC patients, it is difficult to predict the treatment-related toxicity. Especially for PD-1/PD-L1 targeting approaches, there are no clinical studies in lung cancer patients that provide reliable safety and toxicity data. Apart from mere toxicity, missing the optimal radiotherapy fractionation regime to be combined with pharmacological immunotherapy appears to be an issue of concern. A recent report about patients with metastatic solid tumors showed abscopal responses in as many as 22% of NSCLC patients when hypofractionated radiotherapy (single dose: 3.5 Gy) was combined with granulocyte-macrophage colony-stimulating factor based immunotherapy [24]. In this study, grade 3–4 toxicity occurred in about 20% of all patients. Additionally, one patient suffered from grade 4 pulmonary embolism. Van den Heuvel et al investigated the effect of irradiation of NSCLC metastasis in conjunction with an immune-stimulating fusion peptide (NHS-Interleukin-2) [32]. The radiation dose regimen was identical to the FORCE trial (5 × 4 Gy), and no toxicity was observed that could not be explained by the safety profile of Interleukin-2 (e.g. grade I-II thyroiditis in 25% of study subjects). Most clinical data about toxicity from combined modality regimes are derived from retrospective CTLA-4-targeting melanoma series and comprise autoimmune phenomena (e.g. hypophysitis) and – in case of cerebral radiotherapy – brain necroses [33–35]. In a retrospective study on patients with brain metastasis treated with radio-surgical ablative doses (1 x > 16 Gy) and concomitant PD-L1 immune-checkpoint blockade (nivolumab) no toxicities ≥ grade II were observed, although the brain is a radiosensitive organ [36]. Nevertheless, in the context of the FORCE trial irradiation of vulnerable organs such as brain and lung will not be permitted for safety reasons.

The significance of PD-L1 expression of the tumor is a contentious issue. Data from clinical trials indicate that efficacy may correlate with the PD-L1 expression in the primary tumor, whereas other studies report no correlation [9]. To date, marketing approval of nivolumab for squamous and non-squamous NSCLC does not mandate PD-L1 expression testing, whereas pembrolizumab monotherapy requires testing, and a companion diagnostic has been approved by the FDA. Therefore, further investigation of the role and impact of PD-L1 expression – incorporating the current knowledge – is warranted.

Closely connected to the PD-L1 expression are the underlying immune-biological mechanisms of PD-L1 targeting and the potential immune-stimulating effect of radiotherapy. To this end, a systematic exploration to better understand the immune-mediated tumor-host interaction – and thereby the potential impact of PD-1/PD-L1 antibody-treatment – in a true clinical setting is pivotal. The role of tumor-infiltrating lymphocytes and their functional contribution, the biological prerequisites for an immune-mediated tumor-host interaction, and the general notion of an “inflammatory preponderance” of the tissue surrounding the tumor are questions of immense interest to understand the effect of checkpoint inhibitor treatment [37, 38]. An extensive exploratory translational research program attached to this trial will focus on these potential mechanisms of action and the identification of potential biomarkers.

In summary, the rationale of the FORCE trial can be synthesized into three interconnected goals:
to determine the safety and feasibility of the radio-immunological treatment approach;to increase PD-1 checkpoint inhibitor efficacy in metastatic non-squamous NSCLC by inducing an immune-sensitizing effect (abscopal-like effect) with radiotherapy;to explore the fundamental immunological principles that underlie checkpoint inhibitor efficacy and the immune-stimulating effect of radiotherapy in order to elucidate tumor-host biology and to find potential novel biomarkers.

## Data Availability

Not applicable – as no primary data are contained, generated or analysed.

## Abbreviations

AE: Adverse event
AIO: Arbeitsgemeinschaft Internistische Onkologie
CRF / eCRF: Case report form/electronic case report form
CT: Computed tomography
CTCAE: Common terminology criteria for adverse events
CTLA: T-lymphocyte-associated antigen
CTV: Clinical target volume
ECOG: Eastern Cooperative Oncology Group
EOT: End of treatment
FACS: Fluorescence activated cell sorter
FFPE: Formalin-fixed, paraffin-embedded
GTV: Gross tumor volumes
Gy: Gray
HBV: Hepatitis B virus
HCV: Hepatitis C virus
IHC: Immunohistochemistry
irRECIST: Immune-related response evaluation criteria in solid tumors
ITT: Intention-to-treat
MRI: Magnetic resonance imaging
NSCLC: Non-small cell lung cancer
OAR: Organs at risk
ORR: Objective response rate
OS: Overall survival
PD-1: Programmed death-1
PD-L1: Programmed death-ligand 1
PET: Positron emission tomography
PFS: Progression free survival
PP: Per-protocol population
PTV: Planning target volume
QoL: Quality of life
RECIST: Response evaluation criteria in solid tumors
SAE: Severe adverse event
